## Abstract

**Background:**

Diabetic foot ulcers have a high impact on mobility and daily functioning and lead to high treatment costs, for example, by hospitalization and amputation. To prevent (re)ulcerations, custom-made orthopedic shoes are considered essential. However, adherence to wearing the orthopedic shoes is low, and improving adherence was not successful in the past. We propose a novel care approach that combines motivational interviewing (MI) with a digital shoe-fitting procedure to improve adherence to orthopedic shoes. The aim of this trial is to assess the (cost-)effectiveness of this novel care approach compared to usual care (no MI and casting-based shoe-fitting) in promoting footwear adherence and ulcer prevention.

**Methods:**

The trial will include people with diabetes, with IWGDF Risk categories 1–3, who have been prescribed orthopedic shoes. Participants will be randomized at the level of the podiatrist to the novel care approach or usual care. The primary outcome is the proportion of participants who adhere to the use of their orthopedic shoes, that is, who take at least 80% of their total daily steps with orthopedic shoes. A temperature microsensor will be built into the participants’ orthopedic shoes to measure wearing time continuously over 12 months. In addition, daily activity will be measured periodically using log data with an activity monitor. Data from the temperature microsensor and activity monitor will be combined to calculate adherence. (Re-)experienced complications after receiving orthopedic shoes will be registered. Questionnaires and interviews will measure the experiences of participants regarding orthopedic shoes, experiences of podiatrists regarding motivational interviewing, care consumption, and quality of life. Differences in costs and quality of life will be determined in a cost-effectiveness analysis.

**Discussion:**

This trial will generate novel insights into the socio-economic and well-being impact and the clinical effectiveness of the novel care approach on adherence to wearing orthopedic shoes.

**Trial registration:**

Netherlands Trial Register NL7710. Registered on 6 May 2019

## Administrative information

Note: the numbers in curly brackets in this protocol refer to SPIRIT checklist item numbers. The order of the items has been modified to group similar items (see http://www.equator-network.org/reporting-guidelines/spirit-2013-statement-defining-standard-protocol-items-for-clinical-trials/).

## Introduction

### Background and rationale {6a}

Diabetes mellitus is one of the most common chronic diseases worldwide. The disease currently affects 425 million adults worldwide [1], and this number is expected to increase to 600 million people by 2035, due to population growth and aging [2]. A significant number of people with diabetes have foot ulcers (lifetime prevalence of 19–34%) leading to foot infection, amputation, and hospitalization [3]; immobility; and reduced quality of life [4]. In addition, diabetic foot ulcers account for high costs due to unemployment (loss of productivity) and social isolation, healthcare-related costs due to treatment, hospital admissions, and home care [3, 5–9]. Therefore, prevention of foot ulcers has high priority [3–9].

Early detection of risks, self-management, and protective footwear such as orthopedic shoes are considered essential to prevent re-ulceration [10, 11]. Adherence is crucial because patients who adhere to these strategies have significantly better outcomes than those who do not [12]. However, a randomized trial in The Netherlands found that adherence to orthopedic shoes is rather low, with only 46–49% of patients wearing their orthopedic shoes for at least 80% of daily total steps [13, 14]. Research into interventions to improve this adherence is scarce [15], but the explorative study by Keukenkamp et al. [11] showed that motivational interviewing (MI) has short-term positive effects on adherence. Motivational interviewing increased adherence to orthopedic shoes at home after 3 months from 31% (without MI) to 40% (with MI) indicating the beneficial consequences of this communication method [11]. Well-powered high-quality randomized trials are needed to better inform clinical practice about different methods to improve adherence to wearing orthopedic shoes [11, 12, 16].

The role of people’s motives and reasons for (not) adhere to wearing orthopedic shoes is largely unknown [10, 14, 16, 17] and has not been studied systematically [10, 13, 14]. Waaijman et al. [14] demonstrated some predictive value of lower BMI, severe foot deformity, and more appealing orthopedic shoes on adherence. However, their multivariate prediction model explained only 18% of the variance in adherence. This means that optimizing these predicting factors may have a limited effect on adherence and that other factors have to be taken into consideration for improving adherence substantially. Similar to the study of Waaijman et al. [14], most of the studies on diabetic footwear focused on patients’ physical and clinical characteristics rather than social and psychological factors. Until now, the patient perspective on wearing orthopedic shoes, possible psychological barriers, and living and working environments were neglected in adherence studies. However, clinical practice shows that focusing only on clinical aspects (re-ulcerations) and the quality of orthopedic shoes is not enough to improve adherence to orthopedic shoes: wearing orthopedic shoes also requires intrinsic motivation [18].

To improve motivation and adherence, various authors have recommended a combination of improved education and communication with better-fitting orthopedic shoes [10, 11]. First, an observational study found that higher patient satisfaction with the communication between patients and caregivers was associated with increased long-term use of orthopedic shoes [19]. We believe that such a working alliance can be created via motivational interviewing since “motivational interviewing is a collaborative, goal-oriented style of communication with particular attention to the language of change. It is designed to strengthen personal motivation for and commitment to a specific goal by eliciting and exploring the person’s own reasons for change within an atmosphere of acceptance and compassion” [20]. Keukenkamp et al. concluded that motivational interviewing is a promising method for the given purpose and patient group [11]. However, motivational interviewing requires the caregiver to engage with the patient as an equal partner and to not give unsolicited advice or direct, confront, warn, or instruct the patient. Motivational interviewing requires discipline and self-awareness from the caregiver, and mastering motivational interviewing takes practice and time [21]. Podiatrists work at the front lines of diabetic foot care and work with high-risk diabetic patients and are motivated to help guide patients toward better self-care. However, they do not necessarily have the skills to do so effectively. Gabbay et al. believe that there is a great opportunity for podiatrists to explore motivational interviewing to change patient behavior [22]. This suggests that the shoe-fitting procedure plays an important role in creating a working alliance between patient and podiatrist to increase acceptance of and adherence with orthopedic shoes by shared decision-making embedded in person-centered communication [23].

A second factor to increase adherence may be a better fit of the orthopedic shoes. Although perceived orthopedic shoe comfort was not found to be a predictor of adherence for people with diabetes in a previous study [14], [name] et al. [24] found that all aspects of usability are relevant in relation to the use of orthopedic shoes in people with different pathologies. Therefore, the fit of orthopedic shoes will likely affect the adherence of people with diabetes in practice. Currently, orthopedic shoes are mostly produced using a solid 3D mold known as a “shoe last” [25]. These lasts are traditionally made using casting-based methods. However, casting methods are expensive, time-consuming, and complicated due to constraints imposed by manual measurements of several foot dimensions and manual crafting (trial-and-error) of the shoe last to fit the patient’s foot dimensions [26, 27]. A digital shoe-fitting procedure, using a high-end 3D scanner to scan the foot instead of creating a mold around the foot, might be more accurate, patient-friendly, and time-efficient. In this method, the digital scan of the foot is modeled into a patient-specific last that can be milled by a last-milling machine. Although slowly implemented in clinical practice, improvements in scanning methods are expected to lead to a better fit of the orthopedic shoes and therefore to improve adherence to wearing orthopedic shoes.

The factors reviewed above suggest that a multidisciplinary and biopsychosocial approach can help to improve adherence to wearing orthopedic shoes [28] since different aspects have to be taken into account simultaneously to improve adherence meaningfully. However, there is little knowledge about the effectiveness of interventions, and the cost-effectiveness of the novel care approach (motivational interviewing combined with digital shoe-fitting) has not been studied at all [29]. Therefore, the aim of the current study is to assess the (cost-)effectiveness of this novel care approach compared to usual care (no motivational support and casting-based shoe-fitting) in improving adherence to wearing orthopedic shoes and ulcer prevention. This study will generate insights into the socio-economic impact of the novel care approach on adherence to orthopedic shoes. These are crucial steps toward better ulcer prevention in high-risk people with diabetes and to improve their quality of life.

### Objectives {7}

The primary objective is to compare the proportion of participants who sufficiently adhere to using their orthopedic shoes (that is, who take at least 80% of their total daily steps with orthopedic shoes) between participants receiving the novel care approach which consists of motivational interviewing combined with a new digital shoe-fitting procedure and participants receiving usual care.

The secondary objectives are to compare between the novel care approach and usual care: 1) the level of adherence to the use of orthopedic shoes; 2) change in adherence; 3) total wearing time; 4) the proportion of participants (re-)experiencing complications during 1 year follow-up; 5) the participant-perceived quality of life; and 6) the experiences of participants regarding their knowledge about the aim of orthopedic shoes, their satisfaction with communication with the pedorthist regarding wearing orthopedic shoes, their intentions to change wearing behavior, and their satisfaction with orthopedic shoes; in addition, 7) to determine the experiences of podiatrists regarding their knowledge about MI and their experiences and attitudes toward applying MI in this group of patients; 8) the differences in the application of MI between the MI-trained and non-MI-trained podiatrists; and 9) to calculate the differences in costs between the novel care approach and usual car and to assess 10) the cost-effectiveness of the novel care approach compared with usual care.

### Trial design {8}

A multicenter, cluster-randomized controlled trial with (cost-)effectiveness analysis and qualitative and quantitative process analyses.

## Methods: participants, intervention, and outcomes

### Study setting {9}

People with diabetes treated by a pedorthist of Voetmax Orthopedie, for whom foot care is reimbursed in the Dutch healthcare system, will be recruited at different locations of Voetencentrum Wender and Voetmax Orthopedie, located in the east of The Netherlands. Randomization will be performed at the level of the podiatrists (see the “Sequence generation {16a}” section).

### Eligibility criteria {10}

In order to be eligible to participate in this study, a participant must meet all of the following inclusion criteria:
A clinical diagnosis of diabetes mellitus type 1 or 2Aged 18 years or olderWith or without previous callusWith or without previous ulcersIdentified with risk profiles 2, 3, or 4, according to the “zorgmodule preventie diabetische voetulcera 2014” [30]. Internationally better known as the IWGDF Risk 1–3 [31], see Table 1

**Table 1 Tab1:** Care profiles 2–4 versus IWGDF Risks 1–3 for eligible patients

Care profile	Category	Ulcer risk	Characteristics
2	1	Moderate	LOPS + PAD
3	2	Moderate	LOPS + foot deformity
			PAD + foot deformity
4	3	High	LOPS or PAD, and one or more of the following: - History of a foot ulcer - A lower-extremity amputation - End-stage renal disease

*LOPS* loss of protective sensation, *PAD* peripheral artery diseaseEligible for a prescription of orthopedic shoes

Participants will be excluded when they meet any of the following exclusion criteria:
Did not receive orthopedic shoes, but instead an adaption to confection shoes or semi-orthopedic shoesHave a foot ulcerActive Charcot’s neuro-arthropathyHave a foot infectionUnable to walkUnable to read and understand the study instructions

### Who will take informed consent? {26a}

During a multidisciplinary consultation with the pedorthist and medical specialist, the patient will be asked if he/she decided to participate in this study. If he/she decided to participate, the investigator or the investigator’s representative will ask the patient to sign an informed consent.

All podiatrists will provide written informed consent for contribution to the study. They will be asked by the coordinating investigator.

### Additional consent provisions for collection and use of participant data and biological specimens {26b}

On the informed consent form, participants will be asked if they agree to the storage and use of their personal information for future research on adherence to orthopedic shoes. By signing the informed consent form, participants give permission to inform their podiatrist and pedorthist about their participation in the study and inform them when there are unexpected findings that are or could be important to the health of the participant, record one of the consultations with their podiatrist, for the research team to request medical information from their medical files, and when necessary to share data with the competent authorities. Biological specimens will not be collected for this trial.

### Interventions

#### Explanation for the choice of comparators {6b}

The novel care approach will be compared to the usual care as this is a standard clinical practice in The Netherlands.

#### Intervention description {11a}

##### Novel care approach

Participants will receive a combination of MI by the podiatrist to improve acceptance of orthopedic shoes and adherence, and a new digital shoe-fitting procedure by the pedorthist. When the participant needs orthopedic shoes, the podiatrist will refer the participant to a pedorthist to measure for orthopedic footwear (see Fig. 1 for further details).

**Fig. 1 Fig1:**
[figure not shown]
Novel care approach versus usual care

The new shoe-fitting procedure will consist of using a digital iPad scanner with a scan frame where the foot will be scanned (half-)weight bearing. A calibrated length is used to scale the scan results to absolute dimensions.

##### Usual care

MI is currently not provided in standard clinical practice in The Netherlands. Usual care will consist of foot care from the podiatrist. When the participant needs custom-made shoes, the podiatrist will refer the participant to a pedorthist to measure for orthopedic footwear by a casting-based shoe-fitting procedure [32–35] (see Fig. 1 for further details).

##### Motivational interviewing training of podiatrist

Motivational interviewing entails a number of general coaching principles, such as avoiding argumentation and direct confrontation, but rolling with the existing reservations and supporting self-efficacy, optimism, and behavioral intentions in patients to support the change of behavior with regard to wearing orthopedic shoes [20]. A certified MI trainer (Motivational Interviewing Network of Trainers (MINT)) will be training the podiatrists in MI during a 3-day basic training. The podiatrists will be trained to incorporate the specific coaching and communication techniques of MI in their consultation hours with the aim to increase adherence to wearing orthopedic shoes in our target group.

### Criteria for discontinuing or modifying allocated interventions {11b}

Participants can leave the study at any time for any reason if they wish to do so without any consequences. The investigator can also decide to withdraw a participant from the study for urgent medical reasons. The outcomes will no longer be collected, and participants’ data that have been collected up to that moment will be included in the analysis. If participants drop out of the study, additional participants will be included until *N* = 220.

Given the low risk of the intervention, there are no criteria set for premature termination of the study, because this is not to be expected.

### Strategies to improve adherence to interventions {11c}

All participants will be contacted by the coordinating investigator before all their consultations during the study to remind them about the consultation and to bring their orthopedic shoes equipped with a temperature microsensor. If they received questionnaires and/or an activity monitor during the consultation, and this is not returned in 2 weeks after the consult, the participant will be contacted by the coordinating investigator to fill in the questionnaires and return them and/or return the activity monitor.

### Relevant concomitant care permitted or prohibited during the trial {11d}

All participants are allowed to receive any form of (foot) care that they need, e.g,. regular appointments with a podiatrist and/or diabetes pedicure, if necessary wound treatment at a multidisciplinary diabetic foot clinic, and regular appointments with the a pedorthist regarding their orthopedic shoes. This (foot) care will be measured with the iMCQ (Institute for Medical Technology Assessment (iMTA) Medical Consumption Questionnaire).

### Provisions for post-trial care {30}

The multicenter sites have a liability insurance which is in accordance with article 7 of the WMO [36]. This insurance provides cover for damage to research subjects through injury or death caused by the study. The insurance applies to the damage that becomes apparent during the study or within 4 years after the end of the study. There are no other provisions for post-trial care.

### Outcomes {12}

The primary outcome is the proportion of participants who adhere to wearing their orthopedic shoes (see the “Proportion participants being adherent” section). We define adherence as minimally 80% of daily steps taken with orthopedic shoes based on the data of a randomized trial in The Netherlands [13, 14].

Secondary outcomes are 1) the level of adherence to wearing orthopedic shoes during 1 week at 3 and 6 months after inclusion; 2) the change in adherence between 3 and 6 months after inclusion; 3) total wearing time during 1 year follow-up; 4) the proportion of participants (re-)experiencing complications during 1 year follow-up; 5) the participant-perceived quality of life at inclusion and 3 and 6 months after inclusion; 6) the experiences of participants regarding their knowledge about the aim of orthopedic shoes, their satisfaction with communication with the pedorthist regarding wearing orthopedic shoes, their behavioral intentions, and their satisfaction with orthopedic shoes, at inclusion and 6 month after inclusion; 7) the experiences of podiatrists regarding their knowledge about motivational interviewing and their experiences and attitudes toward applying motivational interviewing in this group of patients, after all participants are included; 8) the application of motivational interviewing; and 9) foot care-related costs during 1 year follow-up. For an overview of all time points, see Table 2 (see the “Participant timeline {13}” section).

**Table 2 Tab2:**
[figure not shown]
Overview of the measurements of the study parameters during the study

*Abbreviations*: *EQ-5D-5L* 5-Level EuroQol Quality of Life Scale, *iMCQ* iMTA Medical Consumption Questionnaire, *iPCQ* iMTA Productivity Cost Questionnaire, *m* months, *MOS* Monitor Orthopedic Shoes post-part, *RAND-36 V2.0* Research and Development 36-item Health Survey version 2.0, *wk* weeks

^1^The participants, who will not be approached for the in-depth interview, will be asked to fill in MOS

^2^The iPCQ will also be taken from participants after (re-) experiencing complications; taken 4 weeks after the complication was diagnosed

^3^Activity registration during 1 week

[37] [38] [40] [42] [44] and [47]

#### Proportion participants being adherent

The main study parameter is the proportion of participants who adhere to wearing their orthopedic shoes, defined as minimally 80% of steps taken with orthopedic shoes. The level of adherence (see the “Level of adherence to orthopedic shoes” section) will be based on log data from temperature microsensors in the orthopedic shoes and data from the activity monitors provided to all participants over two 1-week periods measured at time point “T1” and time point “T3” (Table 2). The proportion of adherent participants will be objectively determined based on the combined level of adherence of the two measurements (the mean of time point “T1” and time-point “T3”).

#### Level of adherence to orthopedic shoes

The level of adherence to the use of orthopedic shoes will be determined by the percentage of total steps during the full recording period that the orthopedic shoes were worn and will be calculated as follows:
$$ \mathrm{Adherence}=\frac{\Sigma \kern0.5em \mathrm{steps}\ \mathrm{wearing}\ \mathrm{orthopaedic}\ \mathrm{shoes}}{\Sigma \kern0.5em \mathrm{steps}}\times 100 $$

Total steps wearing orthopedic shoes will be based on log data from temperature microsensors in the orthopedic shoes of all participants, and total steps will be based on using the data from the activity monitors over two times 1 week period measured at time point “T1” and time point “T3” (Table 2).

Adherence to wearing orthopedic shoes and daily step count will be assessed using raw data from the temperature microsensors using and processed by MATLAB (The MathWorks Inc., Natick, MA, USA). Participants will be included in the analyses only if at least four complete days of recording, including one weekend day, are available [14]. When both the temperature microsensor and the step activity monitor show activity during recording, it will be assumed that the participant walked with the orthopedic shoes. If only step activity is recorded, it will be assumed that the participant was walking barefoot or walking in non-prescribed shoes.

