#### Time point “T0”—receiving the first pair of orthopedic shoes (baseline)

Two to 3 months after the multidisciplinary consultation, the participant will receive their first pair of orthopedic shoes during a consultation with the pedorthist. A temperature microsensor (Orthotimer®) is embedded in the insole of the orthopedic shoes for determining adherence by measuring and recording wearing time.

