#### Time point “T2”—receiving the second pair of orthopedic shoes

To deliver the second pair of orthopedic shoes, a regular consultation will be made with the pedorthist 3 months after receiving the first pair of shoes. The second pair of shoes will also be provided with a temperature microsensor (Orthotimer® microsensor) embedded in the insole of the orthopedic shoes. During this consult, the temperature microsensor of the first pair of shoes will be read out with the reading device (Orthotimer® readerdevice) by the investigator.

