##### Orthotimer® and reader device

The Orthotimer® microsensor (Rollerwerk Medical Engineering & Consulting, Balingen, Germany) will be used for continuous, long-term measurement of adherence and is a valid sensor to measure temperature in footwear [45]. The microsensor measures the temperature within the footwear every 15 min (96 measurements per day) and stores these data for 100 days before overwriting the oldest data. Longer observation periods will be possible by reading out the temperature microsensor data before this deadline. Every temperature microsensor reading will be stored with a date- and timestamp. In case participants will be prescribed more than one pair of orthopedic shoes, in both pairs of shoes, a temperature microsensor will be placed and data from both temperature microsensors will be combined.

The temperature microsensor is controlled with the wireless reading device and the saved wearing time dates are transferred to the respective software. The reading device can be connected with the computer via a USB plug. The software is used to control the temperature microsensor as well as to perform the wearing time analysis of the participant data.

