## Discussion

Currently, there is little knowledge about the effectiveness of interventions, and the cost-effectiveness of the novel care approach (motivational interviewing combined with digital shoe-fitting) has not been studied at all [29]. Therefore the aim of this randomized controlled trial is to assess the (cost-)effectiveness of this novel care approach compared to usual care in terms of adherence to wearing orthopedic shoes and ulcer prevention. Since the start of including the first participants in our study, we improved and modified our initial protocol based on operational and logistic issues and new insights; the most important changes are described and explained below.

As in any trial, patient recruitment is crucial. Based on the abovementioned power analysis the required sample size, including the loss to follow-up, for this study was estimated at 220 participants. These participants were to be included in a period of 9 months throughout The Netherlands. However, for practical reasons, it was not feasible to include throughout The Netherlands, and therefore inclusion will only take place in the east of The Netherlands. Because of this change and the outbreak of COVID-19, the goal of 220 participants is no longer realistic with the initially defined criteria and design in the intended period. In order to include as many participants as possible, we were forced to make some changes to the original study protocol.

First, we no longer include only patients receiving their first pair of orthopedic shoes, but we also include patients who already had orthopedic shoes and are eligible for a new pair of orthopedic shoes. Therefore, the pedorthist is now also actively involved in participant recruitment.

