Second, due to this new role of the pedorthist, the background assignment of the treating podiatrist (being trained in MI or not) no longer determines the shoe-fitting procedure by the pedorthist. Each pedorthist has his/her own procedure of shoe-fitting: the new digital shoe-fitting procedure or the casting-based shoe-fitting procedure. In addition, the existing last is also used for an extra pair of orthopedic shoes, and thereby the shoe-fitting procedure is already determined for each subsequent pair of orthopedic shoes. However, the background assignment of the treating podiatrist remains leading over the shoe-fitting procedure with regard to which group the participant belongs to (intervention or control group), because most participants have been treated by the same podiatrist for years and we do not want to change that for this study. The participants in the intervention group will have an appointment with their podiatrist or one of the other MI-trained podiatrists to perform motivational interviewing before or as soon as possible after they receive their first or new pair of orthopedic shoes.

Last, the second group of 12 additional podiatrists received MI training, and 16 podiatrists have been added to the control group to further increase inclusion. Because the inclusion in the intervention group lagged behind the control group, the second group of podiatrists, who received MI training, consists of the podiatrists who see most patients with diabetes. This is in contrast to the original group of podiatrists, who were assigned to one of the groups based on stratified randomization.

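### The adherence scoring rule was not revised when repeat users became eligible: unless their older orthopedic pairs also carry a sensor, steps in them are scored as non-adherent

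*Protocol article*

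**What the plan says.** All references are to the protocol article.

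- **Outcome.** The section on the proportion of adherent participants sets the cut: adherent is "defined as minimally 80% of steps taken with orthopedic shoes", using the mean of two one-week recordings.
- **Scoring rule.** The section on the level of adherence divides steps in orthopedic shoes by all steps. For the numerator: "When both the temperature microsensor and the step activity monitor show activity during recording, it will be assumed that the participant walked with the orthopedic" footwear. For everything else: "If only step activity is recorded, it will be assumed that the participant was walking barefoot or walking in non-prescribed shoes".
- **Sensors.** At T0: "A temperature microsensor (Orthotimer®) is embedded in the insole of the orthopedic shoes for determining adherence". At T2: "The second pair of shoes will also be provided with a temperature microsensor". The Orthotimer section adds: "In case participants will be prescribed more than one pair of orthopedic shoes, in both pairs of shoes, a temperature microsensor will be placed", with the data from both combined.
- **Amended population.** The Discussion drops the restriction to first pairs: "we also include patients who already had orthopedic shoes and are eligible for a new pair of orthopedic shoes". In explaining why the fitting method may already be fixed, it adds that "the existing last is also used for an extra pair of orthopedic shoes".

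The Discussion lists further consequences of the changes, down to visit and questionnaire timing. It does not return to the scoring rule or say how orthopedic shoes owned before enrolment are handled.

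**The concern.** The rule infers footwear from the absence of a sensor signal. That inference is sound only if every orthopedic pair in use carries a sensor. Under the original design this held, since both pairs a participant received came with one. A repeat user may still own a wearable older pair. If it has no sensor, steps in it stay in the denominator, leave the numerator, and are labelled barefoot or non-prescribed although the shoes were prescribed.

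At stake is the primary outcome. The error runs one way, towards lower measured adherence, and a hard cut at 80% turns modest use of an older pair into a change of category. If repeat users are equally common in both arms, the absolute difference shrinks and power falls. If they are not, part of any observed difference could come from the mix of users. The level of adherence and total wearing time rest on the same sensor data and share the gap.

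**Working it through.** **1. The plan's own figure.** Inputs from the sample size section: 40% versus 60%, two-sided alpha 0.05, power 0.80, intraclass correlation 0.01. The sequence generation section gives 20 podiatrists; 10 per arm is assumed. With unpooled variance:

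- n per arm before clustering = (1.960 + 0.842)² × (0.24 + 0.24) / 0.20² = 94.2
- cluster size m = 94.2 × 0.99 / (10 − 94.2 × 0.01) = 10.29
- total = 20 × 10.29 = 205.9

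The stated 200 is within 3% of this and is taken as reproduced. Power at 200 is 0.790 with unpooled variance. The pooled-variance test, used in step 3, gives 0.778.

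**2. Threshold for one participant.** Let a be true adherence (steps in any prescribed orthopedic pair over all steps) and s the share of orthopedic steps taken in a pair without a sensor, treating the two weeks as one. Under the written rule, measured adherence = a × (1 − s). It falls below 0.80 when s > 1 − 0.80/a.

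| True adherence a | Scored non-adherent when s exceeds |
|---|---|
| 100% | 20.0% |
| 95% | 15.8% |
| 90% | 11.1% |
| 85% | 5.9% |
| 80% | 0% |

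Example: a = 100% and s = 25% is measured as 75%, so non-adherent. No value of s raises measured adherence.

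**3. Effect on the comparison, equal mix.** The article gives neither the share of repeat users (r) nor the fraction of truly adherent repeat users pushed below 80% (q). Both are assumptions, shown as a range. Each arm's rate is multiplied by (1 − r × q). Power is at N = 200 with design effect 1 + 9 × 0.01 = 1.09, pooled test.

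| r | q | 1 − rq | Control | Novel care | Power |
|---|---|---|---|---|---|
| 0 | 0 | 1 | 40.0% | 60.0% | 0.778 |
| 0.25 | 0.10 | 0.975 | 39.0% | 58.5% | 0.757 |
| 0.50 | 0.25 | 0.875 | 35.0% | 52.5% | 0.669 |
| 0.75 | 0.50 | 0.625 | 25.0% | 37.5% | 0.446 |

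**4. Effect if the mix differs.** Assume no true effect, 50% truly adherent in each arm, and repeat users forming 30% of one arm and 70% of the other. The spurious difference is 0.50 × (0.70 − 0.30) × q = 0.20 × q: 2, 5 or 10 points for q = 0.10, 0.25 or 0.50. Its sign depends on which arm has more repeat users.

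**The case against.** **Sensors in older pairs are not ruled out.** No sentence says that a pre-enrolment pair goes without a sensor, and the adherence section speaks of sensors in the shoes of all participants. The article is condensed, and the full protocol may contain arrangements for repeat users. This stands: the lack of a sensor is inferred, so the point must be conditional. But the Orthotimer wording looks forward to pairs yet to be prescribed and says both, which matches the two trial pairs. A rule that the article itself states, and leaves unchanged for a changed population, is also more than an omitted detail.

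**The older pair may be out of use.** A patient eligible for a new pair may be replacing a worn one, and the remark about an extra pair is made while discussing lasts. This also stands in part. It bears on size; an extra pair does suggest that replacement is not the only case.

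**The outcome might mean the study pair.** How the shoe is made is part of the intervention. If only trial pairs are the target, steps in an older pair belong outside the numerator and only the label is loose. The article does not define the outcome that way; it refers throughout to orthopedic shoes and contrasts them with non-prescribed footwear. The ambiguity is itself a reason to define the target.

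**Bias between arms.** A reader might infer that bias is likely, because pedorthists now recruit, the added MI-trained podiatrists were chosen for high diabetes volume, and allocation is not concealed. The documents do not support that strength. They give no repeat-user share by arm, the wider eligibility is not described as specific to one arm, and podiatrists were added to both arms (12 MI-trained, 16 control). Imbalance is possible, no more.

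**Conclusion.** The point holds conditionally. If repeat users wear an older orthopedic pair without a sensor during the monitor weeks, the stated rule scores prescribed footwear as non-adherent. The direction is certain and the individual thresholds (20%, 11.1% and 5.9% at true adherence of 100%, 90% and 85%) follow from the rule alone.

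The size in this trial cannot be derived from the article. The range in steps 3 and 4 rests on assumed values of r and q and, for step 4, on an assumed imbalance; none of those figures should be read as an estimate. A reader should also not conclude that older pairs are known to lack sensors, or that the comparison is known to be biased.

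It deserves correction because it touches the primary outcome, inclusion is described as ongoing, and the remedy is inexpensive.

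**What to change.** 1. In the section on the level of adherence, state that steps in any prescribed orthopedic pair count towards the numerator, whether the pair was delivered in the trial or owned before.
2. For participants not yet measured, place a sensor in each older orthopedic pair still worn during the two monitor weeks. Failing that, ask when the activity monitor is returned whether an older pair was worn.
3. For participants who wore an older pair without a sensor, replace the blanket assumption: footwear during step-only activity is unknown, not non-prescribed.
4. Add first-time versus repeat user as a fixed effect in the primary GLMM. History of orthopedic shoe use is already recorded at inclusion.
5. Run a sensitivity analysis in first-time users, or in those reporting no older-pair use. The first is cleaner, because prior use is fixed at inclusion whereas older-pair use is behaviour after allocation.

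Two tempting remedies should be avoided. Telling participants which shoes to wear in the monitor weeks would alter the behaviour being measured. Dropping older-pair days as not evaluable would run into the four-complete-days rule and remove repeat users selectively from an intention-to-treat analysis.

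**Cost:** a few extra sensors, one question and one model term. For participants already measured, only the covariate and the analysis in first-time users remain. The covariate handles a difference in mix between arms but does not undo misclassification, and the restricted analysis has fewer participants and less power.
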